### Perspectives

Increased knowledge of the role of motor skills in the development of wellbeing and insight into the protective potential of early motor skills training could aid in both the future development of high quality preschool care and more specifically target interventions for children with poor motor skills.

**WP 7: Motor Skills and Effects on Executive Functions**

### Background

It is well established that cognitive ability is a powerful determinant of success in many aspects of social and economic life (e.g. Cunha and Heckman 2007; Duckworth et al. 2011). However, more recent research suggests that non-cognitive abilities (e.g. conscientiousness, grit, and self-control) in early life are at least as important as cognitive abilities for later outcomes such as school readiness and educational careers (e.g. Duckworth et al. 2011). Based on recent literature on child development, Cunha and Heckman (2007) found that non-cognitive abilities have direct effects on wages (controlled for schooling), teenage pregnancy, smoking, crime, performance on achievement tests and many other aspects of social and economic life.

The concept of ‘non-cognitive skills’ has been used broadly about skills other than academic skills such as literacy and numeracy. We focus on the link between motor skills and one important aspect of non- academic skills: executive functions, which cover both working memory (which is related to IQ) and inhibitory control, which includes inhibition of thoughts, attention and behaviour (Almlund et al. 2011; Diamond 2014a). We focus on executive functions because most prior work on the non-academic effects of motor skills interventions focuses on executive functions. Within executive functions, we focus on inhibitory control because it is related to concepts such as conscientiousness and self-control that are highly predictive of many long-term outcomes (see Almlund et al. 2011 for a comprehensive review of this literature). Among the big five personality traits, conscientiousness is the strongest predictor of long-term outcomes (Heckman and Kautz 2012). It has been defined as “consistency of action resulting from deliberate volition, or will” (Almlund et al. 2011, p. 10). Conscientiousness is a measure of whether the child manages to accomplish more work, makes an effort, pushes her/himself hard to succeed, is good at organizing, is good at avoiding distractions, does not put off unpleasant tasks, makes careful decisions, is goal-oriented, does not give up easily, remains calm under pressure and the like (MacCann et al. 2009).

Other related traits are grit and self-control (Almlund et al. 2011). Self-control is also highly predictive of a broad range of long-term outcomes even after controlling for academic skills (Moffitt et al. 2013). Although operational definitions of self-control vary widely, Duckworth and Kern (2011) argue that a central commonality is: *“(…) the idea of voluntary self-governance in the service of personally valued goals and standards”* and the *“(…) capacity of altering one’s own responses, especially to bring them into line with standards such as ideals, values, morals, and social expectations, and to support the pursuit of long-term goals”* (Duckworth and Kern 2011, p. 260).

Importantly, recent studies suggest that non-cognitive skills are not innate, but malleable and teachable (Cunha and Heckman 2007; Diamond 2014b). Yet, skills acquired in one period persist into future periods – and skills produced in one period raise the productivity of investments in subsequent periods.

Research implies that better fine and gross motor skills in themselves improve attention, working memory, disciplined action, joy, pride, and social bonding – besides the more obvious improvement of physical wellbeing and fitness (Bugge et al. 2015; Diamond 2014b; Diamond and Lee 2011). The relationship between motor skills and non-cognitive abilities has mainly been studied in small-scale studies in the USA. Despite promising initial results (e.g., Diamond and Lee 2011), the research in this area is still in its early stages with little systematic evidence. In our review of recent literature, we found only seven studies

analyzing the benefits of motor skills interventions (see Table 1 for an overview of the seven studies)1. Of these studies, only one (i.e., Lakes et al. 2004) studies preschool children and most of the studies include small samples of children.

### Table 1: Overview of previous physical studies (RCTs) with self-control related measures as one of their outcome measures

| **Study** | **Type of physical intervention. Type of motor skill in primary focus (fine, gross or balance). Age group. Country.** | **Main results regarding self-control** |
| --- | --- | --- |
| **Sørensen, Mona Have (2015): ”Aktiv Matematik i 1. Klasse. Et skolerandomiseret kontrolleret studie.” in *Rapport for ”Forsøg med Læring i Bevægelse”,* edited by Anna Bugge and Karsten Froberg, Syddansk Universitet, Institut for Idræt og Biomekanik.** | Physical activity in math lessons. Gross motor skills (an active break every 20 minutes throughout the math lesson, making the children able to better concentrate on math after raising the activity level). 6-7-year olds.  Denmark. | Small benefits of exercise on boys’ executive function. |
| **Davis, Catherine L. et al. (2011): *Exercise Improves Executive Function and Achievement and Alters Brain Activation in Overweight Children: A Randomized Controlled Trial. Health Psychol.,* 30: 91-98.** | Aerobic exercises selected based on ease of comprehension, fun, and eliciting intermittent vigorous movement.  Gross motor skills (focus on intensity through activities such as running, basketball, and soccer). 7- 11-year olds. USA. | Benefits of exercise on executive function. |
| **Kamijo, Keita et al. (2011): *The effects of an afterschool physical activity program on working memory in preadolescent children. Dev. Sci.,* vol. 14.** | Physical activity based on improvement of especially cardiorespiratory fitness through engagement in a variety of activities. Gross motor skills (cardiorespiratory fitness). 7-9 year olds.  USA. | Benefits of exercise on Sternberg task performance. |

1 Most of these studies were found in systematic reviews about self-control interventions for children and youth up till 17 years of age (Oxford 2013; Diamond and Lee 2011; Piquero et al. 2010). Still, some of them were so new that they have not been reported in systematic reviews.

| **Weis, Robert, and Toolis, Erin E. (2009): *Evaluation of a voluntary military-style residential treatment program for youths with conduct problems: 6- and 36-month outcomes*. *Psychological Services,* 6(2):139- 153** | Boot camp training consisting of hard military training and school. Gross motor skills.16-18-year olds. USA. | Six months after treatment, those who completed showed fewer externalizing problems, greater adaptive skills, and better behavioural outcomes. Results were not maintained at 36- month follow-up. |
| --- | --- | --- |
| **Lakes, Kimberley D., and William T. Hoyt (2004): *Promoting self-regulation through school-based martial arts training. Applied Developmental Psychology,* 25: 283-302.** | Tae Kwon Do training. Balance and fine motor skills. Kindergarten through Grade 5. USA. | Benefits of exercise in areas of cognitive and affective self-regulation, prosocial behaviour, and classroom conduct. |
| **Zivin, Gail; Nimr R Hassan, Geraldine F. DePaula, Daniel A. Monti, Carmen Harlan, Kashfia D. Hossain, and Ksai Patterson (2001): *An effective approach to violence prevention: Traditional martial arts in middle school. Adolescence,* 36(143): 443-**  **459** | Koga Ha Kosho Shorei Ryu Kempo training. Balance and fine motor skills. Boys in middle school. USA. | Improvement in self- control appeared. |
| **Manjunath, NK, and S Telles (2001): *Improved performance in the Tower of London test following yoga. Indian J Psysiol Pharmacol,* 45: 351-354.** | Yoga training. Balance and fine motor skills. 10- 13-year old girls. India. | Benefits of exercise on executive function, with improvements most evident when executive function demands were greatest. |
| **Sources:** The American systematic Campbell review from 2010 (Piquero et al. 2010) on self-control interventions for children under age 10 for improving self-control, delinquency and problem behaviours.  - **The American systematic review made by Diamond and Lee in 2011 (Diamond and Lee 2011) on interventions shown to aid executive function development in 4–12-year olds.** - **The Danish systematic Oxford review from 2013 (Oxford 2013) on methods that can improve self-control in 7-17-year olds.** - **An RCT from the recently published Danish report from Southern University (Bugge et al. 2015).** | | |

**Objectives**

1. To investigate whether a motor skills intervention improves the preschool children’s executive functioning, especially in terms of self-control and inhibitory control.
2. To investigate the effect of a motor skills intervention on academic performance.

### Variables

*Predictors:*

Gross and fine motor skills as described in the main protocol.

*Outcomes:*

The Preschool Self-Regulation Assessment Battery (PSRA)

The PSRA was designed to assess self-regulation in emotional, attentional, and behavioural domains by using a brief, structured battery of tasks in conjunction with a global report of children’s behaviour. This test can easily be translated into Danish. It includes balance beam and pencil tapping. Age span: 3-5 years. Time consumption: Four brief tasks; 8-10 minutes (Smith-Donald et al. 2007).

Academic performance

Academic performance will be assessed based on the Grade 9 school examinations school grades and the Danish National Test. The Danish National Tests are described in work package 5. Grades from all six subjects in the Danish National Test from Grade 2 to Grade 8 will be used.

### Covariates,

The following covariates will be accounted for when analysing the results: sex, age, socioeconomic status, baseline estimated general intelligence and child wellbeing.

Reynolds Intellectual Screening Test (RIST)

RIST is developed to provide a quick and reliable measure and is used to measure an estimated general intelligence at baseline. The RIST consist of two of the subtests from Reynolds Intellectual Assessment Scale (RIAS). The four RIAS subtests to measure general intelligence include two nonverbal tests and two verbal tests. The RIST consists of one verbal test (Guess what) and one nonverbal test (Odd item out). The test is appropriate for individuals ages 3 to 94. The median reliability coefficient for the RIST Index is .95 and the test-retest reliability is .84 (Reynolds & Kamphaus, 2003). RIAS has been found to correlate highly with the other assessments of general intelligence (Edwards & Paulin, 2007) and there is a high correlation between RIST and RIAS (Reynolds & Kamphaus, 2003).

### Length of follow-up,

The duration of the follow-up period is six months to three years (preschool period)

### Analyses

Simple univariate statistics will be calculated to describe the outcomes and covariates by school.

Multilevel linear regression models will be constructed to assess the effectiveness of the intervention on executive functioning. The baseline value of the outcome variable, time since baseline, intervention group and the covariates of sex, age, estimated general intelligence, socioeconomic status of the household and child well-being at baseline will be added to the model along with school and socioeconomic status of the area as random effects. The interaction between school and intervention group will be tested. The assumptions for the models will be checked.

Similarly multilevel linear regression models will be constructed to assess the effectiveness of the intervention on academic performance as measured by the Grade 9 examination grades. The baseline value of the outcome variable, time since baseline, intervention group and the covariates of sex, age, estimated general intelligence, socioeconomic status of the household and child well-being at baseline will be added to the model along with school and socioeconomic status of the area as random effects. The interaction between school and intervention group will be tested. The assumptions for the models will be checked.

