## Analyses of effect

Simple univariate statistics will be used to describe the outcomes and covariates by preschool. Bivariate analysis adjusted for the design effect will be done to determine if there were any imbalances in the baseline covariates among the two groups.

Multilevel linear regression models will be constructed to assess the effectiveness of the intervention on motor skill performance. The baseline value of the outcome variable, time since baseline, intervention group and any imbalanced covariates will be added to the model along with preschool and socioeconomic status of the area as random effects. The interaction between preschool and intervention group will be tested. The assumptions for the models will be checked.

Multilevel ordinal regression models will be constructed to assess the effectiveness of the intervention on the parents’ perception of their child’s motor competence. The baseline value of the parents’ perception, time since baseline, intervention group and imbalanced covariates will be independent variables. The school and socioeconomic status of the area will be entered as random effects and the interaction between school and intervention will be tested. The model’s assumptions will be tested.

The above analyses will be repeated on a subsample of children who were considered to have a ‘poor’ level of motor competence at baseline.

An analysis will be conducted to determine if the children who dropped out of the study were different from those who remained, based on the baseline values of the outcome variables and the covariates.

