## Perspectives

The Svendborg City Council has granted generous resources to educate the staff; the staff at the preschools is eager to participate; the preschool teachers have contributed to the design of the intervention, ensuring a sense of ownership and involvement; and there is experience with conducting large, cluster randomised controlled trials in the Municipality. Therefore, the conditions for implementation of the intervention in the preschools are optimal. Consequently, if we cannot show an improvement in the children’s motor skills using this framework, further allocation of resources to programs to improve motor development in preschools should probably be discontinued.

On the other hand, if the intervention does succeed, the program can easily be applied in other Danish municipalities due to the design, where each preschool applies the intervention principles in a way to suit their individual conditions regarding physical environment, staffing, etc.

Finally, if the intervention improves motor competence in the children with the highest need for improvement, targeted interventions could be considered if, in some settings, prioritizing of resources is necessary.

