### Analyses

For the RCT study, multilevel linear regression models will be constructed to assess the effectiveness of the intervention on psychological wellbeing. The baseline value of the outcome variable, time since baseline, intervention group and any imbalanced covariates will be added to the model along with preschool and socioeconomic status of the area as random effects. The interaction between preschool and intervention group will be tested. The assumptions for the models will be checked. Similar multilevel linear regression models will be constructed for both the child’s physical and emotional wellbeing and self-esteem. Measures for both groups at baseline and at following points of data collection will be further analyzed using linear mixed effects models (random coefficient models and multilevel models).

The above analyses will be repeated on the children who were considered to have a ‘poor’ level of motor skills at baseline.

In addition to the WP1 analysis of the covariates, an analysis will be conducted to determine if the children who dropped out of the study were different from those who remained, based on the baseline values of the outcome variables.

For the cohort study, longitudinal latent class analysis and latent class growth analysis will be conducted to describe the developmental patterns of wellbeing.

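### The WP 7 model for Grade 9 grades has one undefined 'school' random effect, although each child then belongs to both a preschool and a later school

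*Protocol*

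**What the plan says.** The Analyses section of WP 7 has two model paragraphs. The first is for executive functioning, measured in preschool. The second opens with the word similarly, is meant to "assess the effectiveness of the intervention on academic performance as measured by the Grade 9 examination grades", and repeats the first almost word for word. Both enter the baseline value, time, arm and covariates "along with school and socioeconomic status of the area as random effects", and both test a school-by-intervention interaction. Neither paragraph says which institution the term refers to, and neither has a second institutional level.

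The WP 7 Variables section states where the later outcome comes from: "Academic performance will be assessed based on the Grade 9 school examinations school grades and the Danish National Test". The Perspectives section of WP 1 states where the intervention is delivered: "each preschool applies the intervention principles in a way to suit their individual conditions".

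The document's use of the word is mixed. In WP 1 and WP 6 the parallel linear-model sentence reads "along with preschool and socioeconomic status of the area as random effects". The WP 1 ordinal model, for a parental rating collected before the child leaves preschool, instead says "The school and socioeconomic status of the area will be entered as random effects and the interaction between school and intervention will be tested". WP 7 also describes its data with "Simple univariate statistics will be calculated to describe the outcomes and covariates by school", where WP 1 has preschool in the matching sentence.

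**The concern.** The arm comparison rests on differences between preschools, because whole preschools deliver the programme. Any variance between preschools that persists to Grade 9 therefore belongs in the standard error of the effect. The Grade 9 school is a second source of variance. It is only partly aligned with the preschool, because children from one preschool go to different schools and each school takes children from several preschools.

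One random effect can represent only one of the two. Leaving out the Grade 9 school costs precision. Leaving out the preschool makes the interval too narrow. Since the text does not say which is meant, the choice could be made years later, with the grades already at hand.

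**Working it through.** **Which reading does the text favour?**

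- *For preschool:* the second paragraph is tied to the first by the word similarly, and in the first paragraph the outcome is a test for ages 3–5, so the term there must mean preschool. The WP 1 ordinal model uses the word in the same way. The arm comparisons in WP 3 also adjust for school, most naturally in that sense.
- *For the later school:* WP 7 speaks of preschool children and the preschool period but of Grade 9 school examinations. The follow-up sections of WP 3, WP 5 and WP 8 set three years in preschool against nine years in school.
- *Sign of unadapted text:* the Grade 9 model still asks for a baseline value of the outcome, which a preschool child cannot have for Grade 9 grades.

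The preschool reading is the more natural one, but the text does not settle it.

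**Inputs.** The document gives no number of preschools, cluster size, ICC or feeder pattern for this model, so there is no planned figure to reproduce. All values below are assumed.

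- *Set 1:* 20 or 40 preschools, 20 or 40 children each, 12 Grade 9 schools, school ICC 0.08, 30% or 80% of a preschool's children going to a common feeder school; 1000 null trials per setting.
- *Set 2:* 30 preschools of 20 children, 10 schools, school ICC 0.05, 30–70% of children leaving the feeder school; 500 or 1000 null trials per setting.

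The area socioeconomic random effect and the covariates were not simulated.

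**Term = Grade 9 school, preschool omitted.** With m children per preschool and persisting preschool ICC ρ, the model's standard error is too small by a factor of about r = √(1+(m−1)ρ). A nominal 5% test then rejects with probability of about 2·(1−Φ(1.96/r)).

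| ρ | m | 1+(m−1)ρ | r | approx. type I error | simulated |
|---|---|---|---|---|---|
| 0 | any | 1.00 | 1.00 | 5.0% | 4.8–6.8% (set 1); 4.1% (set 2) |
| 0.01 | 20; 40 | 1.19; 1.39 | 1.09; 1.18 | 7.2%; 9.6% | 7.0–9.7% (set 1); 8.6–9.8% (set 2) |
| 0.02 | 20 | 1.38 | 1.17 | 9.5% | 7.6–9.6% (set 2) |
| 0.05 | 20; 40 | 1.95; 2.95 | 1.40; 1.72 | 16.0%; 25.4% | 15.7–26.6% (set 1); 13.4–16.2% (set 2) |
| 0.10 | 20; 40 | 2.90; 4.90 | 1.70; 2.21 | 25.0%; 37.6% | 24.7–38.2% (set 1); 25.4–26.8% (set 2) |

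Formula and simulation agree. ICC 0.02 was simulated only with 20 children per preschool; for 40 the formula gives r = √1.78 = 1.33 and about 14%. A high share of children going to one feeder school did not remove the inflation.

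**Term = preschool, Grade 9 school omitted.** In set 1 the ratio of true to model standard error was 0.94–1.05 and type I error 4.4–7.4%. In set 2 type I error was 3.6–6.5%. The standard error is therefore not materially understated. The cost is precision: in set 2 the true standard error was about 3–10% larger than with crossed effects. A strong feeder pattern costs more. In set 1, with 40 preschools of 40 children, preschool ICC 0 and an 80% feeder share, the true standard error was 0.083 with preschool only against 0.052 with Grade 9 school only, which is the correct model at that ICC: 0.083/0.052 = 1.60.

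**Both terms, crossed.** In set 2, with a t reference on preschools minus 2 degrees of freedom (30 − 2 = 28), type I error was 3.0–5.8% for preschool ICC 0 to 0.10. A further check under assumed inputs gave about 5–7%, with a true standard error about 3–32% below that of the preschool-only model.

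**The case against.** A reader might infer that the model as written clusters on the Grade 9 school and therefore understates the error of the effect. The document does not support that. The second paragraph inherits a term that means preschool in the first, WP 1 uses the word in the same sense, and nowhere is the Grade 9 school named as a clustering unit. On the inherited meaning the test is roughly valid and only precision is lost. This objection stands, and the point is worded accordingly.

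The inflation figures can also be challenged. They apply only to the less natural reading, they vanish if no preschool variance persists to Grade 9, and the unmodelled covariates and area effect might absorb part of that variance. This stands too, so the figures show what the ambiguity could cost and do not predict how the plan will behave.

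It may be said that such detail belongs in the statistical analysis plan. That would hold if the protocol were silent, but it fixes a random-effects structure for this outcome, and that structure has room for only one of two memberships.

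Finally, this file states delivery by preschool and does not spell out the unit of randomisation, which may be in the main protocol. The recommendation assumes allocation by preschool. WP 1 and WP 6 name the preschool in their linear models and are cited for contrast, not as further instances. WP 7 specifies no between-arm model for the National Tests, so the point covers Grade 9 grades only.

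**Conclusion.** The point holds as an ambiguity with a measurable cost. The Grade 9 model takes over a preschool random-effects structure with a single undefined term.

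On the more natural reading the arm comparison is roughly valid, with a true standard error about 3–10% larger than necessary in most assumed settings and more where feeder patterns are strong and the school ICC is higher. On the other reading, type I error is about 7–10% at a preschool ICC of 0.01–0.02 and 13–27% at 0.05, with no material inflation at 0.

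These sizes rest on assumed cluster counts, ICCs and mixing, without covariates or the area effect. The need to define the term does not depend on them.

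**What to change.** In the second model paragraph of the WP 7 Analyses section, replace school with preschool attended at allocation and Grade 9 school, entered as crossed random effects. State that the intervention effect is tested with degrees of freedom based on the number of preschools, and name the preschool in the interaction sentence as well.

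This is a change of wording. Preschool is known from allocation, and Grade 9 school should come with the grade. The price is a slightly more complex model. In the settings tried it kept type I error at about 3–7% and was more precise than preschool alone.

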60. obtaining reference data on motor skills according to the MABC-2 motor skills test battery. Such reference
61. data is valuable for future surveillance and screening purposes. Thus, an additional aim of this WP is to
62. establish a population-based set of motor skill data to provide standards for interpreting values of motor
63. skills by age and sex.
64. **Objectives**
65. Collectively, the objectives of this WP are:
66. 1. To examine the effect of a three-year motor skills intervention program on short-term (<3-year)
67. changes in objectively measured physical activity and body composition in children attending preschool
68. 2. To examine the effect of a three-year motor skill intervention program in preschool children on longterm
69. changes in objectively measured physical activity and sports participation from preschool age to
70. preadolescence
71. 3. To elucidate the possible bi-directional association between motor skills and objectively measured
72. physical activity and sports participation during preschool and in preadolescence
73. 4. To establish population-based reference data on motor skills according to age and sex
74. **Variables**
75. The outcome measures for this WP are objectively measured physical activity and obesity. A description of
76. the methods to assess motor skills and body composition is provided in the main protocol.
77. *Assessment of physical activity*
78. Habitual physical activity will be assessed at baseline, and at 18 and 30 month.
79. Detailed, objective information on the whole spectrum of behaviours (from sleep-cycle to vigorous activity) will be assessed by continuous 24-hour/6 day Axivity® accelerometer measurement using simultaneous thigh and lower back positioned monitors. The method is an age adjusted version of the method used by Skotte et al. (2014) which provides the ability to classify postural allocations like sitting, lying and standing and activities like walking and running with high sensitivity and specificity (7).
80. The Axivity® AX3 monitor is a small (23 x 32.5 x 7.6 mm), lightweight (11 g), waterproof, 3-axis accelerometer data logger (Axivity, 2016). The monitors will be attached on the child´s right thigh and to the right on the lower back using an allogenic adhesive patch to enable full 24-hour recordings.

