81. Compared to previously used methods using this method will likely improve compliance rates, improve the control of non-wear time and the quality of measurement since the accelerometer keeps the same position on the body and follows the movement of the body. This method has previously been applied in 900 Danish children 9-14 years of age (8).
82. The instrument will be attached to the body using skin-friendly and permeable adhesive patches. If the children participating in this project have eczema or other skin problems, they will be offered to wear an instrument in a belt.
83. We have previously used accelerometers to assess physical activity among large groups of children in this age-group (9-11). The monitors will be initialized to record data during six consecutive days in raw sampling format, which makes it suitable for detecting the short bursts of activity that are typical of preschool children. Sports participation will be obtained from school age using parental-reported SMS as described in WP 3 and previously obtained in the CHAMPS-DK study (12).
84. *Analysis plan*
85. Mixed model linear regression will be used to compare 3-year changes in physical activity and adiposity
86. between children in the intervention group and control group with appropriate adjustment for imbalanced
87. covariates and baseline levels of the outcomes. Bi-directional association between motor skills
88. development and change in physical activity and sports participation will be analyzed in a cohort approach
89. using mixed model regression with adjustment for experimental allocation group and other putative
90. determinants of motor skills and physical activity.
91. Annually obtained information on motor skills will be used to calculate percentile curves for motor skills
92. from age 3 to 5 years to illustrate the developmental course and provide age- and sex-specific variability in
93. a community-wide sample of apparently healthy children.
94. **Primary responsibility**
95. Associate [name] (Head of Research Unit for Exercise Epidemiology and Research in
96. Childhood Health), Department of Sports Science and Clinical Biomechanics, University of Southern
97. Denmark.
98. **References**
99. 1. Burgi F, Meyer U, Granacher U, Schindler C, Marques-Vidal P, Kriemler S, et al. Relationship of physical
100. activity with motor skills, aerobic fitness and body fat in preschool children: a cross-sectional and

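### WP 7 adjusts Grade 9 grades for a baseline value that cannot exist and ends follow-up in preschool; WP 4 has lesser mismatches between its change analyses and its measurement schedule

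*Protocol*

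**What the plan says.** **WP 7.** The second objective is the effect of the motor skills intervention on academic performance. Under Variables: "Academic performance will be assessed based on the Grade 9 school examinations school grades and the Danish National Test". On the latter, "Grades from all six subjects in the Danish National Test from Grade 2 to Grade 8 will be used". Under Analyses, a multilevel linear model is to "assess the effectiveness of the intervention on academic performance as measured by the Grade 9 examination grades. The baseline value of the outcome variable" is then listed first among the terms, followed by time since baseline, group, sex, age, estimated general intelligence, household socioeconomic status and child well-being. The list is the same as for the executive-function model in the preceding paragraph. Under Length of follow-up: "The duration of the follow-up period is six months to three years (preschool period").

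**WP 4.** On accelerometry: "Habitual physical activity will be assessed at baseline, and at 18 and 30 month". On analysis: "Mixed model linear regression will be used to compare 3-year changes in physical activity and adiposity" between the groups. The first objective is "To examine the effect of a three-year motor skills intervention program on short-term (<3-year") changes. The second asks for long-term change in objectively measured activity and in sports participation, from preschool age to preadolescence. On the latter measure: "Sports participation will be obtained from school age using parental-reported SMS as described in WP 3".

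**The concern.** A baseline-adjusted model needs the outcome, or a named substitute, measured before randomisation. For Grade 9 grades there is none, so whoever runs the analysis must depart from the stated model. That decision would fall years later, with outcome data in hand, and one available choice is harmful. An early National Test score looks like a natural baseline, but it is itself a possible result of the intervention. Adjusting for it could remove part of the effect under study and would forfeit the protection of randomisation.

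The follow-up statement adds to the problem. Read literally, WP 7 stops observing children before any of its academic outcomes is recorded.

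In WP 4 less is at stake. The time point of the activity contrast is mislabelled, and one long-term change has no starting value.

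**Working it through.** No figure in the plan needs reproducing. The check compares what each analysis requires with what the file says is measured.

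**WP 7, Grade 9 model**

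1. Required: an academic value before randomisation in preschool.
2. Listed academic measures: National Tests in Grades 2 to 8 and the Grade 9 examinations.
3. The earliest is Grade 2, which follows both preschool and the intervention. Baseline academic values available: none.
4. The executive-function model uses the same covariate list. There it makes sense: the PSRA covers ages 3 to 5, so a preschool baseline is possible. The sentence appears to have been carried over to an outcome that it does not fit.

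**WP 7, follow-up**

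1. Stated: at most 3 years, all in preschool.
2. Required for the second objective: up to Grade 9. WP 3, WP 5, WP 8 and the cohort part of WP 6 give this span as three preschool years plus nine school years, 3 + 9 = 12 years.
3. Shortfall: 12 − 3 = 9 years, that is, all of the school years. Even the Grade 2 test lies outside the stated period.

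**WP 4, activity change**

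1. Listed times: 0, 18 and 30 months. WP 1 places the 18-month visit in spring 2018, so baseline is about autumn 2016 and 30 months about spring 2019. WP 1 also gives 30 months as its longest follow-up.
2. A 3-year change needs 36 months; 36 − 30 = 6 months beyond the last listed measurement.
3. The schedule supports changes over 18 and over 30 months. Both are under three years and agree with the first objective.

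**WP 4, second objective**

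1. A change in sports participation from preschool age needs a preschool value. Collection starts at school age, so there is none.
2. A long-term change in objectively measured activity needs accelerometry in preadolescence. This file lists nothing after 30 months.

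**The case against.** The strongest reply is that much of this is loose wording. In part that is right.

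- **3-year changes.** The programme is called a three-year one, and other work packages speak of three years in preschool. The label may simply mean the preschool period, with 30 months as its last visit. A reader might infer that the WP 4 activity effect cannot be estimated. It can: a mixed model on baseline, 18 and 30 months is estimable once the time points are named. The same sentence covers adiposity, whose assessment is described in the main protocol, so the mismatch is shown for activity only.
- **Long-term activity.** This file is an addendum to a main protocol that is not shown and may schedule later accelerometry. The statement must stay at what is listed here.
- **School as random effect.** A reader might take this to mean the later school in the Grade 9 model and conclude that clustering by preschool is ignored. The text does not support that. WP 1 uses school for preschool in its model of the parent rating, which is collected before the child leaves preschool. The WP 7 executive-function model does the same for a preschool-age measure. Nor does the file give an intracluster correlation or cluster size from which to size such an error.
- **Share reaching 30 months.** WP 1 allows 6 to 30 months of follow-up, so some children leave earlier. No entry-group sizes are given, so no share can be derived.
- **National Tests.** A reader might say that they are never modelled. WP 5 models their reading scores, though not as intervention effects, and a separate WP 7 effect model may be left to an analysis plan.

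None of this touches the baseline term or the follow-up statement in WP 7.

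**Conclusion.** The WP 7 point stands on the text alone. The Grade 9 model contains a term for which no child can have a value, and the stated follow-up stops before any academic outcome occurs. A stated trial objective therefore cannot be analysed as written. Removing the term leaves an estimable model, so the defect lies in the specification; the data planned for Grade 9 are not in question.

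The WP 4 point is smaller. It consists of a 6-month gap between the label and the last listed activity measurement, a change in sports participation without a starting value, and a long-term activity objective with no matching measurement in this file. The last item depends on the main protocol.

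The conclusion rests on the measurement times listed here and on reading a baseline value as one taken before the intervention. It makes no claim about the school random effect, a variance inflation or the proportion of children seen at 30 months. The primary outcome, MovementABC-2 at 18 months, is not affected. The correction should be made, but it does not threaten the trial's main result.

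**What to change.** **WP 7**

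- Delete the baseline-outcome term from the Grade 9 model and enter baseline PSRA in its place. Baseline estimated general intelligence is already a covariate and needs no addition. A PSRA baseline is implied by the executive-function model; confirm it against the main protocol.
- State that no test score obtained after randomisation is used as a baseline.
- Keep the preschool follow-up for the first objective and extend the stated follow-up to Grade 9 for the second.

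**WP 4**

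- Restate the activity analysis as change from baseline to 18 and to 30 months.
- Restate the sports part of the second objective as a between-arm comparison of level, or trajectory, during school age.
- For objectively measured activity in the second objective, reconcile objective and schedule with the main protocol: either cite the later measurement or limit the objective to 30 months.

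The cost is wording; the restated analyses need no data beyond those already planned. The downside is that the long-term change claim in WP 4 becomes narrower.
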